## Abstract

**Introduction:**

Cardiac rehabilitation (CR) is offered to reduce the risk of further cardiac events and to improve patients’ health and quality of life following a cardiac event. Psychological care is a common component of CR as symptoms of depression and/or anxiety are more prevalent in this population, however evidence for the cost-effectiveness of current interventions is limited. Metacognitive therapy (MCT), is a recent treatment development that is effective in treating anxiety and depression in mental health settings and is being evaluated in CR patients. This protocol describes the planned approach to the economic evaluation of MCT for CR patients.

**Methods and analysis:**

The economic evaluation work will consist of a within-trial analysis and an economic model. The PATHWAY Group MCT study has been prospectively designed to collect comprehensive self-reported resource use and health outcome data, including the EQ-5D, within a randomised controlled trial study design (UK Clinical Trials Gateway). A within-trial economic evaluation and economic model will compare the cost-effectiveness of MCT plus usual care (UC) to UC, from a health and social care perspective in the UK. The within-trial analysis will use intention-to-treat and estimate total costs and quality-adjusted life-years (QALYs) for the trial follow-up. Single imputation will be used to impute missing baseline variables. Multiple imputation will be used to impute values missing at follow-up. Items of resource use will be multiplied by published national healthcare costs. Regression analysis will be used to estimate net costs and net QALYs and these estimates will be bootstrapped to generate 10 000 net pairs of costs and QALYs to inform the probability of cost-effectiveness. A decision analytical economic model will be developed to synthesise trial data with the published literature over a longer time frame. Sensitivity analysis will explore uncertainty. Guidance of the methods for economic models will be followed and dissemination will adhere to reporting guidelines.

**Ethics and dissemination:**

The economic evaluation includes a within-trial analysis. The trial which included the collection of this data was reviewed and approved by Ethics. Ethics approval was obtained by the Preston Research Ethics Committee (project ID 156862). The modelling analysis is not applicable for Ethics as it will use data from the trial (secondary analysis) and the published literature. Results of the main trial and economic evaluation will be published in the peer-reviewed National Institute for Health Research (NIHR) journals library (Programme Grants for Applied Research), submitted to a peer-reviewed journal and presented at appropriate conferences.

**Trial registration number:**

ISRCTN74643496; Pre-results.

Strengths and limitations of this studyA prospectively designed within-trial economic evaluation alongside a randomised controlled trial, with comprehensive data collection.Supplemented by an exploratory decision analytical model to assess cost-effectiveness over a longer time horizon.Comprehensive sensitivity analysis will be used to explore a range of alternative measures of health benefits, impact of assumptions and time horizons.Data limitations, such as the trial time frame, are likely to affect the plausibility of long-term results.Issues with generalisability due to variations across cardiac services and populations entering cardiac rehabilitation.

## Introduction

In the UK approximately 90 000 people start cardiac rehabilitation (CR) annually, receiving a supervised programme of care that aims to improve patients’ health and quality of life.^1^ The population offered CR is variable; the British Association for Cardiovascular Prevention and Rehabilitation propose three groups of priority, including acute coronary syndrome, coronary revascularisation and/or heart failure, with further groups who should be offered CR if possible (including stable angina among others).^2^ The greatest number of attendees of CR in the UK come from populations with myocardial infarction, percutaneous coronary intervention, coronary artery bypass graft and heart failure.^1^ The reported benefits of CR include reduced mortality, reduced hospital admissions, improvements in patient cardiovascular risk profiles and improved psychological well-being and quality of life.^3^ Around 50% of those offered CR attend.^1^

The latest figures suggest that in the UK around 18% and 28% of patients initiating CR have borderline or clinical depression and anxiety, respectively.^4^ Rehabilitation programmes vary, most frequently including lifestyle risk factor management (eg, physical exercises) and health behaviour change and education.^3^ Guidelines also recommend that a psychological component is included in CR care.^3^ Despite this, current interventions (including pharmacological and psychosocial interventions) have been shown to have limited effectiveness in this group.^5^ Psychological components of CR have been less frequently analysed in cost-effectiveness evaluations and results of cost-effectiveness studies are varied.^6^ Research to determine whether psychological therapy is effective and cost-effective in CR is a priority, given recent calls for closer integration of psychological and physical health outcomes.^7^

Metacognitive therapy (MCT) may be well-suited to the needs of CR patients; it is based on the metacognitive model, which proposes that a thinking style dominated by rumination, worry and threat monitoring maintains emotional distress.^8–10^ MCT is highly effective at reducing this thinking style and alleviating symptoms of depression and/or anxiety in mental health settings and may therefore have the potential to improve health in the CR population.^5 11 12^ There are no existing published economic evaluations of MCT.

The PATHWAY Group MCT multicentre, single-blind, randomised controlled trial aims to evaluate the effectiveness and cost-effectiveness of group-based metacognitive therapy for CR patients with elevated anxiety and/or depressive symptoms.^5^ Details of the main trial study protocol are available elsewhere.^5^ In brief, participants were recruited from patients with heart disease and referred for CR, in five UK National Health Service (NHS) Trusts. Trial participants had to meet CR eligibility criteria, score 8 or more on either the anxiety and/or depression subscale of the Hospital Anxiety and Depression Scale (HADS), be aged 18 years old or more and able to read, understand and complete questionnaires in English. Patients who gave informed consent to participate in the trial completed baseline assessments and were randomised via telephone link to Manchester Clinical Trials Unit. Participants were allocated to the intervention/comparator arms in a 1:1 ratio via a minimisation algorithm (incorporating a random component) to maximise balance between the two arms on gender, HADS score and hospital site. Participants randomised to the intervention arm received 6 weekly sessions of group-based metacognitive therapy delivered by either CR professionals or research nurses. The intervention and control groups were both offered in the usual CR programme within their Trust. The primary outcome is severity of anxiety and depressive symptoms at 4-month follow-up measured by the HADS total score.^13^ Secondary outcomes are severity of anxiety/depression at 12-month follow-up, health status, severity of post-traumatic stress symptoms, strength of metacognitive beliefs and service use at 4-month and 12-month follow-up. The PATHWAY Group MCT trial is part of a wider NIHR (National Institute for Health Research) programme grant for applied research, which began in August 2014 and with an end date of February 2021.

The aim of the economic evaluation component of the PATHWAY Group MCT trial is to estimate the cost-effectiveness of the addition of MCT intervention to CR for patients with elevated anxiety and/or depression symptoms, in a UK setting from a health and social care perspective. This will consist of a within trial analysis using patient-level data collected during baseline and follow-up study time points, and an economic model synthesising data from the trial and wider literature.

## Methods and analysis

The economic evaluation of group MCT in CR will comprise of two analyses; a within-trial economic analysis prospectively designed to assess cost-effectiveness for the duration of the trial (12 months) and an economic model to explore the potential longer-term cost-effectiveness of MCT in this population and in different populations and settings.

Both analyses will use a cost-effectiveness acceptability analysis to assess the incremental cost-effectiveness of the addition of MCT intervention to the CR for patients with elevated anxiety and/or depression symptoms. The intervention is group-based MCT plus usual CR, and the comparator is usual CR alone. The perspective for the primary analysis (trial and model) is health (NHS) and social care service providers (costs) and CR participants (health benefits), which is the perspective recommended by National Institute for Health and Care Excellence (NICE).^14^ Note that social care in the UK is delivered by a range of providers (public sector, commercial and voluntary) and encompasses a range of social support services.^15^ The work will conform to the NICE recommended methods and will be reported in accordance with the Consolidated Health Economic Evaluation Reporting (CHEERS) statement.^14 16^

### Patient and public involvement

The patient and public involvement (PPI) group from the group MCT trial will be presented with the findings of the economic evaluation and consulted about possible dissemination activities that target patient groups.

### Within-trial analysis

The analysis will use individual patient-level service use and health benefit data from all participants recruited and allocated to a management arm in the PATHWAY Group MCT trial (n=332). The trial opened for recruitment in July 2015 and closed in January 2018, follow-up finished in February 2019. The economic analysis of trial data will begin in April 2020 and will complete by September 2020. The analysis will compare the addition of group-based MCT to usual CR versus usual CR alone (standard practice) for individuals with elevated symptoms of depression and/or anxiety. The study sample for the economic evaluation is all participants randomised to receive the group-based MCT plus usual CR, or usual CR only. In brief, participants were people eligible and offered (referred to) CR as per NHS trust protocol, with a HADS score of 8 or more on the anxiety and/or depression subscale. The intervention, usual care and participant inclusion and exclusion criteria are summarised and described in detail in the trial protocol.^5^ Usual CR (dependant on NHS site) includes varying degrees, psychological interventions to address distress such as relaxation, stress management and some cognitive challenging.

The time horizon of the within-trial primary cost-effectiveness analysis will be 12 months, to incorporate sufficient time for any impact of MCT on service use, subsequent costs and health benefit. This differs to the primary clinical effectiveness time horizon, which will be 4 months (note, a sensitivity analysis will look at cost-effectiveness at 4-month follow-up).^5^

#### Outcomes

The measure of health benefit for the primary analysis will be the quality-adjusted life-year (QALY). This will be estimated from the EQ-5D-5L health status measure completed at baseline and 4-month and 12-month follow-up. The EQ-5D is a validated, generic health status measure, allowing for the comparison of health benefits across different disease areas. The EQ-5D has been shown to be a valid and responsive measure of health in CR patients.^17^ Furthermore, the QALY and the EQ-5D are the measures recommended for economic evaluations by NICE.^18^

The EQ-5D-5L captures the following five domains of health status: mobility, self-care, usual activity, pain/distress and anxiety/depression. Each domain is rated on a 5-point scale of levels: no problems, slight problems, some problems, severe problems or unable to do activity. Resulting health status profiles will be converted to utility values using the published utility tariffs and methods recommended by NICE at the time of analysis. An EQ-5D-5L valuation set is available that reflects the preferences of members of the public in England for health states defined by the EQ-5D-5L.^19^ However, concerns have been raised during the quality assurance of this value set and currently, NICE recommend that the crosswalk algorithm used to map from the EQ-5D-3L to the EQ-5D-5L continues to be used.^20^ The economic evaluation will use the value set recommended by NICE at the time of analysis. The use of alternative value sets will be investigated in the sensitivity analysis.

Total QALYs will be estimated as follows:

$$QALY=\sum \left(\left[U_{i}+U_{i+1})/2\right]\times (t_{i+1}-t_{i}\right)$$

Here, U=utility value and t=time between assessments. The time between assessments is the time from baseline data collection to follow-up.

#### Resource use and costs

Direct costs will be estimated for the primary analysis. Service use included in the economic evaluation is listed in table 1. With the exception of the intervention and usual care cardiac rehabilitation, data on the healthcare resources used for each participant were collected from an economic patient questionnaire at baseline and follow-up (4 and 12 months). The questionnaire was adapted from surveys used by the authors in previous trials.^21–24^ The changes to the questionnaire were developed with the service user group and the clinical experts in the research team. The questionnaire was pilot tested before use. At baseline this is completed by the participant with assistance from a researcher. This means participants have experience of completing it once with help before they need to complete it unassisted. At follow-up participants complete the questionnaire on their own but were aware a researcher could help them complete the questionnaire if needed. A copy of the questionnaire is provided in the online supplementary material and has been uploaded to the Database of Instruments for Resource Use Measurement (DIRUM).^25^ The questionnaire asks patients to report service use for the follow-up period (time since the last questionnaire or 3 months at baseline) and for the last month. If a participant struggles to recall service use for the full follow-up but knows the last month, this is included to help prompt the participant. For the primary analysis, participants with 1-month but not the full assessment period service use data will be treated as having missing data. The missing data will be imputed using the multiple imputation process defined for all participants with missing data. Two sensitivity analyses will explore the impact of using the 1-month recall data (see table 2).

10.1136/bmjopen-2019-035552.supp1Supplementary data

**Table 1 T1:** Economic evaluation service use measures

Service type	Unit measure
**NHS healthcare use (collected by a self-report economic patient questionnaire**)	
Hospital inpatient	Days per stay
Hospital day	Number of visits
Hospital outpatient	Number of visits
Accident and emergency	Number of visits
Primary care*	Number of visits
Community care†	Number of visits
**Metacognitive therapy (collected by the trial team**)	
Staff time (cardiac rehabilitation nurse, cardiac nurse, physiotherapist or occupational therapist)	Number of hours
Paper manual	By unit
CD exercise	By unit
**Cardiac rehabilitation attendance (collected by the trial team**)	
Exercise cardiac rehabilitation	Number of attendances
Education cardiac rehabilitation	Number of attendances

*Examples include general practitioner.

†Examples include community-based mental healthcare and social support.

CD, compact disk; NHS, National Health Service.

**Table 2 T2:** Within-trial sensitivity analysis

Assumptions/variables	Changes	Rationale
Missing data are assumed to be missing at random	Complete case analysis Pattern mixture approach	The complete case analysis will use only the observed data and will provide insight to the result for the group of participants with complete follow-up and complete data (evaluable cohort). The pattern mixture approach will assess the impact of assuming that compliance and clinical outcomes are systematically worse in people with missing or with incomplete follow-up. It will be assumed that these differences will also lead to systematic worse health benefits and higher costs for participants with missing data^26 28^ The results of the complete case and pattern mixture analyses will be compared with the primary analysis based on multiple imputed data sets to give an indication of how robust the cost-effectiveness estimate is to assumptions about missing data.
Use of 1-month recall data	Assume that service use is equally distributed over the assessment period and that the 1-month data can be multiplied up to 4-month or 8-month follow-up. Add the 1-month cost estimates to the multiple imputation process, depending on the pattern of missing data and sufficient participants with both 1-month and 4-month or 8-month cost estimates.	The primary analysis treats the 1-month service use data as uninformative for participants who are missing data for the assessment period. These two sensitivity analyses explore the impact on the results of this approach.
Treatment received rather than intention-to-treat	The MCT group will only include those who attended at least one MCT session	The primary analysis will be an intention-to-treat approach. Recognising that not all patients assigned to the MCT intervention will attend, we will also run an analysis dividing the group using the recorded MCT attendance data.
Subgroup analyses	History of anxiety and depression at baseline Gender HADS at baseline (severity of depression and anxiety)	Subgroup analysis will be conducted if there are enough numbers of participants in each group, to explore how the likely cost-effectiveness differs according to the population. Note, this is highly explorative and will be used to guide the economic model and generate further research questions rather than producing definitive results/conclusions.
Measure of benefit	Hospital Anxiety and Depression Scale (HADS) Cases of anxiety and/or depression Reliable improvement in HADS score Return to productive activity	Secondary analyses will explore the cost-effectiveness of MCT intervention using a problem-specific measure of effectiveness, rather than the generic QALY. This will look at the cost per point change in the HADS, as well as cost per reliable improvement in HADS and cost per case of anxiety and/or depression avoided. Cases of anxiety and depression will be classified using the HADS score (8 to 10=mild, 11 to 14=moderate and 15 to 21=severe).^45^ In our analysis we will focus on the cut-off used in the inclusion criteria for the Group MCT trial (≥8 on either the depression or anxiety subscale of the HADS). Productive activity (employed, voluntary work, in education or training, carer or looking after the family or home). These alternative measures of benefit will be used to aid decision-makers who may be less familiar with QALYs or have different objectives/targets.
Utility value set to estimate QALYs	Alternative EQ-5D value sets (Devlin *et al* 2018^46^; van Hout *et al*, 2012^20^)	Secondary analyses will explore the impact of using alternative value sets to calculate QALYs. The primary analysis will use the value set recommended by NICE at the time of the analysis, the remaining EQ-5D value set will be used in a sensitivity analysis. This will assess the impact of the different methods that can be used to estimate utility.
Cost of MCT intervention	Assumed larger group size Inclusion of wider costs (training and catering)	Sensitivity analysis will be conducted in which a larger average group size is assumed because if MCT was implemented in CR, a larger group size would be likely. Additionally, separately to group size, we will also look at a more comprehensive (although uncertain) method of costing the MCT intervention, which will include staff training costs
Time horizon	4 months	The final trial time follow-up is 12 months. A secondary analysis will consider the 4-month follow-up (the primary follow-up of the trial), to assess the impact of different follow-up periods on cost-effectiveness results.

Adherence to CR has been defined by the study team as the attendance to four or more sessions to each component of usual CR (exercise sessions and educational talks).

CR, cardiac rehabilitation; MCT, metacognitive therapy; QALY, quality-adjusted life-year.

Note that from the reported service use, psychological treatment outside of cardiac rehabilitation and MCT will also be costed. MCT attendance data collected during the trial by the research team will be used to estimate a per participant cost for the MCT intervention. In the primary analysis, this will include staff costs and the cost of materials. The average group size from the trial will be used to calculate a cost per session per participant, which will be multiplied by the number of sessions attended by each participant. Staff time to deliver MCT and attendances at cardiac rehabilitation will be collected by the research team.

The unit costs of NHS and social care services will be derived from national average unit cost data. These unit costs are published annually in the NHS reference costs database, and in the Unit Costs of Health and Social Care document published by the Personal Social Services Research Unit, University of Kent. The price year for all costs will reflect the most recent unit costs at the time of analysis. The total direct costs of service use for each trial arm (including MCT and cardiac rehabilitation) will be estimated by summing the costs of each resource by the reported use to provide health and social care.

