Single imputation will be used to impute missing baseline data. This simple approach is appropriate for baseline data, although in reality this is unlikely to have a significant impact as participants who have missing data at baseline are less likely to have follow-up data.^26 27^ Baseline variables are observed at entry to the trial and vary by the individual rather than random allocation to trial arms or values at follow-up. In contrast follow-up values for clinical and economic measures may be dependent on trial allocation and baseline. Accordingly, single imputation for baseline measures of cost, utility and clinical indicators ensures the estimated values are independent of treatment allocation and follow-up values. Single imputation is likely to be more efficient than multiple imputation. Multiple imputation (MI) will be used to impute missing follow-up data for costs and QALYs, which assumes that the data are missing at random (conditional on observed responses to clinical and economic measures and baseline covariates); MI of both costs and QALYs is recognised as an appropriate approach to deal with missing observation and missing follow-up data.^26^ Missing values will be imputed for each follow-up point. All missing follow-up cost and utility data will be assumed to be missing at random. To make best use of available data, we plan to impute costs by category (inpatient, outpatient and primary/community care) and utility by individual EQ-5D domain (mobility, self-care, usual activities, pain/discomfort and anxiety/depression). A balance is required between including all items and the stability of the imputation model if there is a high level of missing data. The stability of the model reduces as the number of variables with missing data increases. If feasible, all individual items in each cost category will be included in the imputation model. Total costs and QALYs (baseline to follow-up) will be generated using Stata passive estimation commands. The final imputation plan will be refined following a review of missing data (exploration of whether there are any patterns of missingness) and according to the patterns of service use and EQ-5D data. Two sensitivity analyses will explore whether the results vary by approach taken to missing data. The first will use complete case analysis. The second will use a pattern mixture approach that assumes compliance and clinical outcomes are systematically worse in people with missing or with incomplete follow-up.^26 28^ The specification of the analysis will be finalised after review of the complete and missing data patterns and discussion with clinical experts about plausible assumptions. If appropriate this analysis will identify the threshold values of compliance and clinical outcome that would lead to a change in conclusions about the relative cost-effectiveness of the within trial economic analysis.

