
Multiple imputations will be conducted in Stata V.15, using predictive mean matching and sequential chained equations. Regression models used to impute missing data will be based on key covariates associated with costs or health benefits. A long list of potential covariates was identified from a recent systematic review of economic evaluations in the population undergoing cardiac rehabilitation and the baseline data collected within this randomised controlled trial (see online supplementary material). Discussions with clinical experts in the team will be used to assess the relevance and logic of using these variables as covariates in our analysis. This approach will be supplemented with pooled descriptive analyses and regression analyses to identify the final set of covariates.^6^ A list of potential covariates is included in the online supplementary material.

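### The primary analysis ignores reported last-month service use when full-period recall is missing, so an imputed period cost can fall below the cost the participant reported

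*Protocol article*

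**What the plan says.** All references are to the protocol article.

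- **What is collected** (Resource use and costs): each questionnaire covers use since the previous one (3 months at baseline) and, separately, use in the most recent month. Follow-up questionnaires are at 4 and 12 months, so the follow-up windows are 4 and 8 months.
- **Primary rule** (same section): "participants with 1-month but not the full assessment period service use data will be treated as having missing data". The next step is: "The missing data will be imputed using the multiple imputation process defined for all participants with missing data".
- **How that imputation works** (Missing data): it is done "using predictive mean matching and sequential chained equations", by cost category, with individual items added if feasible. No person-level lower bound is stated.
- **How the plan describes its choice** (Table 2, row on 1-month recall data): "The primary analysis treats the 1-month service use data as uninformative for participants who are missing data for the assessment period". The article gives no reason for this premise.
- **Sensitivity analyses** (same row): there are two. The first is to "Assume that service use is equally distributed over the assessment period and that the 1-month data can be multiplied up to 4-month or 8-month follow-up". The second adds the 1-month cost to the multiple imputation, subject to the pattern of missing data and to enough participants having both the 1-month and the period cost.

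**The concern.** The last month is part of the window being imputed. A last-month report is therefore a strong predictor of the period total and a logical minimum for it. The primary analysis uses it as neither. Predictive mean matching copies a donor's observed value. If matching ignores the last-month report, a participant who reported an admission last month can be given a donor with no inpatient cost.

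The primary net cost, and so the incremental cost-effectiveness ratio (ICER), may then rest partly on imputed values that contradict data the trial collected. The missing-at-random assumption, which the Discussion accepts may not be valid, is also weaker than the available data allow.

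The better alternative is only a conditional sensitivity analysis. If its condition is not met, the only remaining analysis that uses the 1-month reports is the flat scaling.

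**Working it through.** The article gives no figure on this point to reproduce. It states the rule, the method and the windows. It does not give visit rates, a time profile of service use, or the number of participants with 1-month data only. The numerical inputs below are assumptions, except the window lengths.

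**1. Windows.** First follow-up window: 4 months. Second: 12 − 4 = 8 months. Both agree with Table 2.

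**2. Lower bound.** Period use = last-month use + use in the other 3 (or 7) months. The second term cannot be negative, so period use ≥ last-month use. This needs no assumption.

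**3. One participant (assumed figures).** A £2,500 admission is reported for the last month and the rest of an 8-month window is not recalled. Suppose 80% of donors have no inpatient cost and 20% have £2,500.

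- True period inpatient cost: at least £2,500.
- Mean imputed cost: 0.8 × £0 + 0.2 × £2,500 = £500. The imputed value is below the reported amount in 80% of draws.
- Flat scaling: 8 × £2,500 = £20,000.

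**4. How often the bound could be broken (simulation, assumed inputs).** Monthly visits are Poisson given a gamma frailty with shape 1. Covariates explain 10% or 30% of the frailty variance. The donor is one of the near neighbours on the covariate score, and the last-month report is not used. The table shows the share of imputed period counts below the reported last-month count, among participants reporting any last-month use; ranges run over the two covariate strengths.

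| Visits per month | 4-month window | 8-month window |
|---|---|---|
| 0.1 | 68–71% | 51–56% |
| 0.5 | 37–41% | 22–26% |
| 1.5 | 25–28% | 14–16% |

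Among all simulated participants, including those reporting no last-month use, the shares are about 6–17% (4 months) and 5–10% (8 months). The problem is greatest for infrequent services, such as admissions, and smaller for frequent contacts.

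**5. Flat scaling.** If monthly use falls geometrically with half-life h months, let r = 0.5^(1/h). For a window of W months:

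scaled ÷ true = W × r^(W−1) ÷ (1 + r + … + r^(W−1))

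For h = 6, r = 0.891. With W = 4: 4 × 0.707 ÷ 3.392 = 0.83.

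| Assumed half-life (months) | ×4 | ×8 |
|---|---|---|
| constant use | 1.00 | 1.00 |
| 12 | 0.92 | 0.81 |
| 6 | 0.83 | 0.64 |
| 3 | 0.68 | 0.39 |
| 2 | 0.55 | 0.22 |

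Scaling is right on average if use is flat and wrong otherwise. The article does not say which applies.

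**The case against.** The strongest defence is that the choice is disclosed and already tested. Table 2 states it openly and plans two analyses to examine it. The second puts the 1-month cost into the imputation and needs no flat-use assumption. The Missing data section warns that the imputation model becomes less stable as incomplete variables are added, and says the plan will be refined once missingness has been reviewed. The pattern mixture analysis also allows for higher costs in participants with missing data.

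Most of this stands, and it makes the point a design weakness rather than a hidden error. It does not remove the point. The second analysis is conditional, has no stated floor and leaves the primary result unchanged. The pattern mixture analysis is not described as using what these participants reported.

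A reader might infer more than the article supports:

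- *That scaling by 4 or 8 is the fallback for the primary analysis.* It is one of two sensitivity analyses.
- *That the plan contradicts its own missing-at-random statement.* The phrase "conditional on observed responses to clinical and economic measures and baseline covariates" describes the assumption in general terms. It does not promise that every collected item is a predictor.
- *That scaling must understate use because cardiac rehabilitation comes early.* Table 1 has rehabilitation attendance recorded by the trial team, outside the questionnaire, so it is not scaled. No time profile is given for the other services.
- *That poor recallers are heavy users, or that net cost is biased in a known direction.* The article gives no data on either.

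**Conclusion.** The point holds as an improvement to make, not as a contradiction. That the primary rule sets aside observed last-month use, and that no stated step stops an imputed period cost from falling below it, follows from the text and simple arithmetic. The planned remedy may not be run, and the other analysis that uses the 1-month reports is unbiased only under flat use.

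The effect on net cost and the ICER cannot be sized or signed. Of the 332 randomised participants, the article does not say how many have 1-month data only or how they divide between arms. The effect could be negligible. The percentages and ratios above are illustrations that rest on assumed rates, covariate strength and time trends.

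**What to change.** 1. In the primary imputation, include the 1-month cost by category as an auxiliary predictor at each follow-up, where enough participants have both measures. Use category totals only if the model is unstable.
2. Do not allow an imputed period cost below the reported 1-month cost in the same category, for example by restricting the donor pool or applying a floor after imputation. The floor is best paired with the predictor: alone, it can only raise costs and makes no use of reports of zero last-month use.
3. Run the present rule, which ignores the 1-month data, as the sensitivity analysis.
4. Where data allow, replace flat scaling with the observed ratio of period to last-month cost, by category and follow-up point, among participants who gave both.
5. If the present primary rule is kept, state why the 1-month data are treated as carrying no information.

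**Cost.** The data are already collected, and the article leaves the final imputation plan open to refinement. The price is a slightly larger imputation model and some extra programming, because a person-specific floor is not part of ordinary predictive mean matching. Steps 1 and 4 both depend on enough participants having reported both periods.
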